### Randomization and allocation

After inclusion, participants are randomized to either EMDR + TAU or “TAU only” by another RA (RA2, a psychologist), not involved in the assessments. Participants are allocated to their treatment condition based on a randomization code. RA2 generates a randomization sequence before the recruitment phase starts using freely available software [45].

The randomization sequence is stratified by participating facility (a total of six sites), further subdivided by a maximum of three care pathway (‘youth’ (youngsters up to 23 years old), ‘addiction’ (adult patients with primarily addiction) or ‘addition, care and housing’ (adult patients with problems on multiple life domains in addition to addiction and often severe psychiatric problems), if there is a participating EMDR therapist available in that striatum. EMDR therapists may work at multiple facilities and/or care pathways and thus see participants from different strata. This amounts to a stratified randomization with a 1:1 group allocation within each stratum, using block sizes of 4.

When participants are allocated to TAU only, no action is taken (since RA1 already planned subsequent assessments, independent of allocation). When they are allocated to EMDR + TAU, RA2 informs participants by email about EMDR with additional written information. RA2 also informs a participating EMDR therapist of the same facility where the participant receives TAU. The EMDR therapist contacts the participant and provides additional information about EMDR to the participant and plans seven weekly EMDR sessions.

Great care is taken so that all those involved in the study are blinded as much as possible. Participants, RA1 (the assessor) and the principal investigator are blinded to group allocation while EMDR therapists are blinded to outcome of assessments. In addition, the principal investigator was not involved in the treatment of participants.

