### Power and sample size calculation

Since two active treatment arms are compared and the sample is expected to be relatively heterogeneous regarding baseline variables such as dependence severity, drinking status and other substance use, it is estimated that the effect size will be relatively small. Clinical relevant differences on the primary outcome variable (changes in number of heavy drinking days in the previous 30 days) were calculated on the basis of data of a recent study [46]. In patients with an alcohol-use disorder referred to in- or outpatient alcohol treatment the mean baseline score for heavy drinking days (≥5 drinks in a single day, over the past 30 days) was 16.33 (SD 11.99). Treatment outcome was such that undertreated patients (<75% attendance of the number of sessions recommended by treatment allocation guidelines, n = 618) showed a reduction of 8.7 heavy drinking days (±12.5) while overtreated patients (>110% attendance of sessions recommended) showed a reduction of 12.5 heavy drinking days (±12.2, n = 362). The difference between under- and overtreated patients is at least 3.8 heavy drinking days over the past 30 days which corresponds to an effect size of *d* = 0.31 or *f* = 0.15).

Subsequent poweranalysis in G*Power version 3.1.2. [47] (ANOVA: repeated measures, within-between interaction) indicated a sample size of 74 to demonstrate this effect (keeping α at 0.05 and power at 0.80 and using 2 groups and 3 measurements (concerning changes in the number of heavy drinking days between 4 time points)). Attrition is estimated to be relatively high at 33%. Therefore we add 26 participants (100 patients in total, 50 in each treatment arm), to meet the required sample size.

To minimize missing values RA1 will use email, text messages, telephone calls, and/or contacts with participants’ regular therapists to remind participants about their assessment appointments. All participants will receive financial compensation of 25 euros (in the form of a gift cheque) for every complete assessment at T2 and T3, regardless of whether or not the participant drops out of treatment.

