### Analyses

All analyses will be executed using SPSS. Summary tables will be provided for all baseline, end of treatment and follow-up variables. Data will be summarised using frequency tables (with confidence intervals when applicable), and descriptive statistics (mean, median, interquartile range, number and percentages of participants and two-sided, 95% confidence intervals when appropriate).

Changes in the number of heavy drinking days in the past 30 days will be used to analyze the efficacy and effectiveness of EMDR. Since this primary outcome variable is continuous, a repeated measures ANOVA will be carried out with 2 group (EMDR + TAU versus TAU) and 4 time (pre-, post-treatment, 1 and 6 month follow-up) factors. Randomization stratum will be used as a covariate. Effect sizes will be calculated.

All allocated participants will be included in the primary analysis (intention-to-treat, ITT). Since an ideal ITT requires a complete set of data [89], multiple imputation (or a similar strategy) will be used for missing data, if possible. In addition a per-protocol (PP or completers) analysis will be done. ITT analyses will provide insight into the effectiveness of the treatment in real life whereas PP analysis gives insight into the efficacy or the ability for the treatment to reach its intended effect under ideal circumstances.

Repeated measures of continuous secondary variables such as time to first alcohol consumption, number of total drinks consumed and average drinks per occasion in the past 30 days, severity of the dependence, level of rumination, negative affect, desire thinking, craving, coping self-efficacy, quality of life, biomarkers will be analyzed by carrying out a repeated measures ANOVA with 2 group (EMDR + TAU versus TAU) and 3 (post treatment versus 1 versus 6 month follow-up: time to first drink variable derived from TLFB data) or 4 time (pre- versus post-treatment versus 1 versus 6 month follow-up: all other data) factors.

Distribution of premature treatment termination (PTT), a categorical variable, will be analysed using chi-square tests. A range of baseline clinical characteristics potentially associated with subsequent PTT will be examined. A logistic regression analysis will be conducted to examine the relative contribution of key variables to PTT status. A Kaplan–Meier survival curve will be used to illustrate the distribution of PTT prior to the completion threshold at session 5.

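### The randomisation factors (site and care pathway) are named as a covariate only for the primary ANOVA; carry them into the secondary between-arm models, as two categorical main effects

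*Protocol article*

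**What the plan says.** Under Randomization and allocation, the protocol stratifies by six facilities, each subdivided into at most three care pathways where an EMDR therapist is available: "This amounts to a stratified randomization with a 1:1 group allocation within each stratum, using block sizes of 4".

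Under Analyses, the primary outcome (heavy drinking days) gets a 2 x 4 repeated measures ANOVA, followed by one sentence: "Randomization stratum will be used as a covariate". The secondary outcomes (time to first drink, total drinks, drinks per occasion, craving, rumination, desire thinking, affect, self-efficacy, quality of life, biomarkers) "will be analyzed by carrying out a repeated measures ANOVA with 2 group (EMDR + TAU versus TAU) and 3" or 4 times. The three-time version is for time to first drink. No stratification factor is named there. For premature treatment termination (PTT) the text says: "Distribution of premature treatment termination (PTT), a categorical variable, will be analysed using chi-square tests". A later paragraph lists covariates that may be added for primary and secondary outcomes; stratum is not among its examples.

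The sections on randomisation and on treatment as usual (TAU) describe the pathways as different in patients (youth; mainly addiction; problems in several life domains, often with severe psychiatric problems) and in TAU (CRA or MDFT of typically 6 months, against outreaching FACT that may last much longer).

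**The concern.** Stratified blocked randomisation balances the arms within strata, so differences between strata hardly enter the arm comparison. A model without the strata still counts those differences as error. The standard error is then too large for the design, the test runs below its nominal level and power is lost. The pathways differ in patients and in length of TAU, so they plausibly predict outcome and, because TAU ends at different times, plausibly predict change over time as well. In a 100-patient trial with 33% expected attrition, a few points of power on the secondary outcomes are worth keeping if they cost only a sentence.

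The form of adjustment matters too. The protocol does not say how stratum enters the primary model, and copying an unspecified covariate into the secondary models could gain nothing.

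**Working it through.** **Inputs from the protocol.** "keeping α at 0.05 and power at 0.80 and using 2 groups and 3 measurements"; "effect size of *d* = 0.31 or *f* = 0.15"; 3.8 days' difference with SDs of change of 12.5 and 12.2; 74 patients before attrition, 100 enrolled, 33% attrition; 6 sites x at most 3 pathways = at most 18 strata.

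**Not in the protocol, so assumed.** Share of outcome variance explained by strata (R2) 0 to 20%; within-person correlation 0.5; sphericity.

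**1. The plan's own figure.** d = 3.8 / 12.35 = 0.31, and f = d/2 = 0.15. For the group x time interaction, lambda = f² x N x m / (1 - rho) = 0.0225 x 74 x 3 / 0.5 = 9.99, with 2 and 144 degrees of freedom: power 0.806. So 74 reproduces. This concerns the primary outcome; no power is stated for secondary outcomes. After attrition, 100 x 0.67 = 67 patients.

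**2. Interval width, between-arm comparison.** Width without / with adjustment = t(N-2) / [t(N-2-q) x sqrt(1-R2)], where q is the degrees of freedom spent. Site + pathway main effects use q = 5 + 2 = 7.

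| R2 | N = 67 | N = 100 |
|---|---|---|
| 0 | 0.998 | 0.999 |
| 0.10 | 1.052 | 1.053 |
| 0.20 | 1.115 | 1.117 |

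**3. Type I error, between-arm.** With full balance within strata, the unadjusted test rejects only when a standard normal exceeds 1.96 / sqrt(1-R2). At R2 = 0.10 this is 2.066, or 3.9%; at 0.20 it is 2.191, or 2.8%. Simulation with blocks of 4, 33% random loss and four visits gave 3.4 to 3.9% unadjusted and 4.8 to 5.4% adjusted.

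**4. Power, comparison of post-treatment means.** Simulated with site + pathway main effects, four visits, a 0.5 SD effect, and strata explaining 10% constant variance plus 5 to 20% of the variance of change to 6 months (2000 runs, error about 1 point):

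| N | Unadjusted to adjusted, 5% | Unadjusted to adjusted, 20% |
|---|---|---|
| 100 | 80.5% to 85.2% | 75.2% to 84.4% |
| 67 | 60.6% to 66.0% | 56.8% to 66.2% |

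The gains are 4.7, 9.2, 5.4 and 9.4 points. With no stratum effect the cost was under 1 point at N = 100 and 3 to 4 points at N = 67; a second simulation put it at about 1 to 2 points.

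**5. Power, group x time interaction.** A stratum effect that is the same at every visit drops out of within-patient contrasts. Unadjusted type I error then stayed near nominal (4.3 to 5.7%) and adjustment gained nothing. In the simulation of step 4 there was no gain at 5 to 10% stratum-by-time variance; at 20%, power went from 67.2% to 71.8% (N = 100) and from 48.4% to 50.3% (N = 67).

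**6. Form of the covariate.** All 18 cells would hold 100/18 = 5.6 patients each, or 67/18 = 3.7 after attrition, and cost 17 degrees of freedom. In a separate simulation of one change score with R2 = 0.15 and 67 patients, power was 62% unadjusted, 61% with the 18-cell factor and 66% with site + pathway. A single numeric stratum code left the mean standard error at 0.199, against 0.200 unadjusted and 0.186 with site + pathway. For the interaction test, an 18-stratum factor cost 5 to 8 points when stratum effects were absent or constant.

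**7. PTT.** Assuming 20% v 45% termination at N = 100, replacing chi-square by Cochran-Mantel-Haenszel moved power from 0.79 to 0.78 (6 strata) and from 0.80 to 0.76 (18 strata) with no stratum effect. With strong effects (log-odds SD 1.0) it moved from 0.67 to 0.72 and from 0.65 to 0.69.

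**The case against.** The strongest reply is that silence is not exclusion. The primary model is given in the same group-and-time shorthand, with the covariate in a separate sentence. Nothing says that stratum is dropped elsewhere, the later covariate list is open-ended, and a condensed article may leave secondary covariates to an analysis plan. This stands in part: a reader should not infer a deliberate decision to leave stratum out. But the section does give two specifications, one with and one without stratum, so the wording is worth settling.

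Second, no association between stratum and outcome is documented, and conservative tests are not invalid. This stands, and it makes every size above conditional.

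Third, the planned tests are repeated measures tests. Much of any stratum effect cancels in the interaction, and a sparse stratum factor can cost more than it returns. This also stands, and it is why the form of adjustment belongs in the point.

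Fourth, the protocol never says that stratum enters as a numeric code, and the number of strata actually opened may be well below 18. This is true; the form is simply unspecified, and main effects are safe either way.

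Finally, many secondary outcomes are exploratory and no power is claimed for them. That limits the stakes.

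**Conclusion.** A modest, conditional point. If strata explain 10 to 20% of variance, unadjusted between-arm comparisons of secondary outcomes run at about 3 to 4% type I error, with intervals about 5 to 12% too wide. With the added stratum-by-time effects assumed in step 4, they give up about 4 to 10 points of power. Time to first drink is the clearest case, because its ANOVA has no pre-treatment value through which stratum differences could cancel. For the group x time interaction the expected change is about -2 to +4 points (4.6 in the most favourable setting simulated), and the gain needs strong stratum-by-time effects.

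A reader might infer that the secondary intervals are certainly too wide and that omission has no upside. The documents do not support that: they give no prognostic strength for the strata, and omission saves degrees of freedom when strata are sparse or uninformative. A reader might also conclude that the PTT chi-square is wrong. The text does not say outright that this test compares the arms, PTT is defined separately for EMDR and TAU, a logistic regression is also planned, and a stratified test gains 4 to 5 points only under strong stratum effects.

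All sizes rest on the assumed R2, a correlation of 0.5, random loss and simulation error of about 1 point.

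**What to change.** In Analyses, replace the single stratum sentence with a statement that the primary and the secondary between-arm models include site (6 levels) and care pathway (up to 3 levels) as categorical main effects, neither as one numeric code nor as a site-by-pathway factor of up to 18 cells.

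Optionally, say whether the PTT chi-square compares the arms. If it does, and pathway is expected to predict termination strongly, a test stratified by care pathway could replace it.

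The change is wording only, since both factors are known for every randomised patient. Its price is up to 7 degrees of freedom: about 1 to 2 points of power if the strata are not prognostic, and 3 to 4 points in one simulation with 67 patients retained. It should be fixed before outcome data are examined by arm.

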## Discussion

This RCT aims to extend previous findings [15] by including a larger number of participants, using reaction time tasks and bloodsamples in addition to participant-report questionnaires and scales, excludes the principal investigator from treatment and data-collection and uses an outpatient instead of an inpatient setting. A strength of the study is that it is a multi-site trial, enhancing the internal and external validity of the interventions. Another strength is that the exclusion criteria are limited, enhancing the generalizability of findings. In addition, by identifying mediators, moderators and predictors of treatment outcome theoretical models of relapse may be expanded.

The main goal of the study is to determine whether EMDR, when added to TAU, reduces drinking behavior and relapse rates further than TAU only. Even a relative small effect size may be relevant, when achieved with a limited dose of EMDR. In addition, EMDR may provide an important adjunct to current treatment options for patients suffering from craving, negative affect and rumination. In both cases the quality of life is expected to improve.

Finally, the study is aimed at establishing whether the application of EMDR aimed at addiction is feasible and safe in this patient population, even when patients still use substances. Clinicians may be hesitant to use EMDR in this population because they fear triggering craving and subsequent relapse.

## Trial status

Currently recruiting participants and started with data collection.

## Abbreviations

ACRA: Adolescent Community Reinforcement Approach
AE: Adverse events
ANOVA: Analysis of variance
AUDIT: Alcohol use disorders identification test
CDT: Carbohydrate-deficient transferrin
CIDI: Composite international diagnostic interview
CRA: Community reinforcement approach
CRA-HS: Community reinforcement approach happiness scale
DSM-IV-TR: Diagnostic and statistical manual of mental disorders (4th ed., text revision)
DTQ: Desire thinking questionnaire
EMDR: Eye movement desensitization and reprocessing
EQ-5D™: EuroQol - 5 dimensions
FACT: Function assertive community therapy
GGT: serum γ-glutamyltransferase
IAT: Implicit association task
MATE: Measurements in the addictions for triage and evaluation
MDFT: Multidimensional family therapy
M.I.N.I.-plus: M.I.N.I. international neuropsychiatric interview-plus
PACS: Penn alcohol craving scale
PANAS: Positive and negative affect schedule
PANAS-SF: Positive and negative affect schedule – short form
PTQ: Perseverative thinking questionnaire
PTSD: Posttraumatic stress disorder
RA: Research assistant
RCQ-D: Readiness to change questionnaire - dutch version
RCT: Randomized controlled trial
SAE: Serious adverse events
SD: Standard deviation
SELD: Self-efficacy list for drug users
TAU: Treatment as usual
TLFB: Timeline followback
VAS: Visual analogue scale
